### Study organization, administration, and governance

The Emilia-Romagna Surgical Colorectal Audit (ESCA) is a multicenter, retro-prospective, observational non-profit study promoted by the IRCCS Istituto Romagnolo per lo Studio dei Tumori (IRST) “Dino Amadori” in Meldola and the Local Health Agency of Romagna (AUSL Romagna).

Members of the surgical units participating in the study contributed to its design gave feedback and reviewed the study protocol. ESCA is overseen by a study steering committee composed of surgeons, epidemiologists, statisticians, IT specialists, and healthcare administrators.

ESCA received a financial support from Johnson & Johnson Medical S.p.a Ethicon Division for data management and monitoring.

The objectives of the study are as follows:To systematically collect data of all patients undergoing surgical treatment for primary CRC from diagnosis up to 6 months after surgery;To evaluate risk adjusted post-operative complications and mortality;To evaluate adherence to the clinical audit activity of each participating center;To evaluate the possible positive effects on outcomes, both clinical and economic, of systematic measurement and monitoring (Hawthorne effect).

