Every 12 months, an anonymized report on volume and KPIs will be delivered to each hospital comparing data of all the participating centers. A set of relevant case-mix variables (patients’ frailty, tumor burden, type of surgery) will be also identified in order to produce a reliable comparison of outcomes between hospitals and give each center case-mix adjusted outcomes.

Data collected during the first 18 months (from April 2019 to October 2020) will be analyzed in order to evaluate preliminary results on primary and secondary outcomes. The first preliminary analysis will be used as benchmark to further implement the auditing activity.

Case-mix adjusted data will be presented using funnel plots with a 95% confidence interval (Fig. 2).

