**Fig. 2 Fig2:**
[figure not shown]
Case-mix adjusted data will be presented using funnel plots with a 95% confidence interval

Reports of the enrolment rate, obtained by comparing the number of enrolled patients to the hospital discharge cards (HDC), will be sent to each center every 3 months. The aim of this feedback activity is to progressively obtain a 100% enrolment of eligible patients and thus provide “real-world data” that avoid bias related to patient selection.

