## Statistical considerations

All the analyses will be performed considering tumor location (colon or rectum) as a stratification factor. For continuous variables, the arithmetic mean and standard deviation (SD), as well as the median value and minimum–maximum, will be presented. Absolute frequencies together with the percentage relative frequencies will be reported while summarizing qualitative variables.

To evaluate the performance of surgical activity, absolute numbers and relative percentages of each performance indicator reported will be calculated. The mortality rate will be defined as the number of patients who died within 30, 90, and 180 days after surgery. Graphical representation will also be used: funnel plots will be displayed for each KPI, both in unadjusted and adjusted versions.

Appropriate statistical models (i.e., mixed models, logistical regression, multilevel models) will be developed to evaluate the relationship among analyzed indicators and potential explanatory factors as well as for standardization/adjustment purposes. Main covariates will include age, gender, ASA score, CCI, surgery setting (urgent vs. elective), and ECOG.

Hospitals will be used as random effects to account for the presence of possible variability among hospitals. Other exploratory subgroup analyses will be performed.

Furthermore, to assess the effects of continuous monitoring and benchmarking on clinical outcomes, a before-and-after approach will be used. Specifically, assuming the time from the first subject surgery until the release of the first benchmarking report as the reference period (baseline, i.e., “before” period), the analysis will evaluate any significant changes occurred afterwards. Any changes on the outcomes will be, therefore, attributed to the benchmarking effect.

Missing values will be replaced and estimated using multiple imputations. A two-sided 95% confidence interval (95% CI) will be reported as appropriate.

Statistical analysis will be performed using R statistical software (v. 4.0.6) — www.r-project.org.

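### The before/after rule credits any change to benchmarking, although secular drift is not separated out and the baseline is already under audit

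*Protocol article*

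**What the plan says.** The section on statistical considerations states that "to assess the effects of continuous monitoring and benchmarking on clinical outcomes, a before-and-after approach will be used". The baseline is defined by "assuming the time from the first subject surgery until the release of the first benchmarking report as the reference period", and everything later is the comparison period. The rule of interpretation follows: "Any changes on the outcomes will be, therefore, attributed to the benchmarking effect". No other part of the article limits it.

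On adjustment, the same section says "Main covariates will include age, gender, ASA score, CCI, surgery setting (urgent vs. elective), and ECOG", and "Hospitals will be used as random effects to account for the presence of possible variability among hospitals".

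The section on key performance indicators and feedback says "Every 12 months, an anonymized report on volume and KPIs will be delivered to each hospital comparing data of all the participating centers". It also says that enrolment-rate reports "will be sent to each center every 3 months", with the aim of moving enrolment step by step to 100%.

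The fourth objective, in the section on study organization, is "To evaluate the possible positive effects on outcomes, both clinical and economic, of systematic measurement and monitoring (Hawthorne effect"). The Introduction describes the mechanism: people who know that they are being monitored change their behaviour.

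**The concern.** There are two separate faults.

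**Drift.** The comparison sets two consecutive blocks of calendar time against each other in the same hospitals. Every hospital receives the reports, so none shows what would have happened without them. The named covariates describe the patient and the urgency of surgery. They cannot remove a trend in technique or perioperative care. Rising enrolment completeness is a further source of change that is not benchmarking. Under the stated rule, all of this is credited to benchmarking.

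**Baseline.** The reference period starts at the first audited operation. Patients are already being registered, and quarterly enrolment feedback is part of the scheme. By the article's own account of the Hawthorne effect, the reference period is therefore exposed to monitoring. The contrast cannot estimate the effect of monitoring that the fourth objective names.

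At stake is a causal statement about auditing, which the Discussion hopes to carry forward into regional and national quality standards.

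**Working it through.** The article gives no sample size, effect size or power for this analysis, so there is no figure of its own to reproduce. The steps below show how far drift alone moves the contrast.

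**Inputs from the article**
- Accrual of about 800 patients per year; 7 hospitals.
- Study length of 54 months as stated; the inclusion dates (15 April 2019 to 31 December 2023) give about 56.5 months.
- Cut point: the reports are annual, but the first preliminary analysis, to be used as benchmark, covers 18 months. Both readings are possible.
- Two-sided 95% intervals.
- Colon cancer mortality of 3.4% at the start of the Dutch audit, used here only as a low event rate.

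**Assumptions**
- True benchmarking effect of zero.
- Steady relative drift of 3% or 5% per year.
- A 15% event rate as a second, higher rate. The article gives no complication rate.

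**Step 1: distance between the periods.** With total length T and cut at c, the midpoints are c/2 and (c + T)/2. Their distance is T/2, whatever c is.
- T = 54: 27 months = 2.25 years.
- T = 56.5: 28.25 months = 2.35 years.

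**Step 2: apparent relative risk with no true effect.** RR = r^(28.25/12), with r the yearly ratio.
- 3% per year: 0.97^2.354 = 0.931.
- 5% per year: 0.95^2.354 = 0.886.

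With 27 months the values are 0.97^2.25 = 0.934 and 0.95^2.25 = 0.891.

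**Step 3: chance of a significant false improvement.** An 18-month baseline gives 800 × 1.5 = 1,200 before. The total is 800 × 56.5/12 = 3,767, which leaves 2,567 after. For a pooled, unadjusted two-proportion test, z = (p1 − p2)/√[p1(1 − p1)/1,200 + p2(1 − p2)/2,567], with p2 = p1 × RR, and the chance is Φ(z − 1.96).

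| Event rate before | Drift per year | Rate after | z | Chance |
|---|---|---|---|---|
| 3.4% | 3% | 3.16% | 0.375 | 5.7% |
| 3.4% | 5% | 3.01% | 0.621 | 9.0% |
| 15% (assumed) | 3% | 13.96% | 0.839 | 13.1% |
| 15% (assumed) | 5% | 13.29% | 1.388 | 28.4% |

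Without drift the chance in this direction is 2.5%. With a 12-month cut the 15% rows become 11% and 23%.

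**Step 4: does a time term help?** A logistic simulation used 3,600 patients over 54 months, 600 runs per scenario, no hospital clustering, a 20% event rate and odds falling 5% per year. The before/after term alone was significant (two-sided) in 20% to 23% of runs. With linear calendar time added, it was significant in 5% to 6%. With no drift, both models gave about 5%.

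**Step 5: the baseline.** This needs no arithmetic. The objective asks for monitored against unmonitored. The defined contrast is monitored without outcome benchmarking against monitored with it. The difference between these two can only be the increment from benchmarking. A time term does not change that.

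**The case against.** The strongest defence is that this is a condensed article. The covariate list names only main covariates, the models are described generically, and a calendar-time term may stand in a fuller plan. That is fair as regards the model. It does not rescue the attribution rule, which the article states outright and which a fuller plan would have to contradict.

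A second defence is that the feedback effect is a secondary outcome. That is correct: the primary objective, the frequency of complications, re-interventions, readmissions and deaths, is untouched.

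A third is that the quarterly reports cover enrolment and not outcomes, so adding outcome benchmarking remains a legitimate contrast. That also stands, and it is why the second fault is limited to the monitoring objective. An exposed baseline tends to shrink a monitoring effect. It does not create the drift bias.

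A reader might infer more than the article supports:

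- **That drift will certainly be reported as an effect.** This holds only if drift exists. Even then, significance is the less likely result in every scenario of the table.
- **That the fall in Dutch mortality gives the size of the drift.** That fall, 3.4% to 1.8% over 8 years or about 7.6% per year, happened within an audit and is cited as its success. Applied to a 15% complication rate it yields 56%, but this joins a mortality trend to an assumed complication rate. At 3.4% the same calculation gives about 15%.
- **That hospital random effects understate the error of the period effect.** The article neither specifies nor excludes hospital-specific changes. This is detail for the analysis plan, and the article gives no figure for such variation.
- **That an unmonitored control series is at hand.** No section shows access to records from before April 2019 or from non-participating hospitals.

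**Conclusion.** The concern holds in two limited parts.

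First, the attribution rule is wrong for an uncontrolled before/after design. Any steady drift enters the benchmarking effect at about 2.25 to 2.35 times its annual size. This factor depends only on study length and on the drift being steady, not on the cut date. The relative risks of 0.93 to 0.89 rest on the assumed drift of 3% to 5% per year. The chances of 6% to 9% and 13% to 28% rest further on the event rates, an 18-month baseline, and a pooled, unadjusted test. The article stratifies by colon and rectum and plans case-mix models. Smaller strata would lower these chances, while the bias from trends in care would remain.

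Second, the analysis cannot answer the objective on monitoring itself. The word retro-prospective might suggest unmonitored early data, but no section describes any, and inclusion starts on 15 April 2019.

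**What to change.** 1. Replace the attribution sentence. State that changes after the first benchmarking report will be reported as associations and that secular trends cannot be excluded.
2. For this secondary question, prespecify a case-mix-adjusted segmented (interrupted time-series) model with a calendar-time trend and a change in level and in slope at the report date. State which report sets that date, since the annual report and the 18-month analysis point to different ones.
3. Restrict the claim to what outcome benchmarking adds to an audit already running, and reword the fourth objective to match.
4. Optionally, where regional administrative data are accessible, use a series from before April 2019 or from non-participating hospitals as a comparator for mortality and readmission. Access, consent and the lack of clinical case-mix variables would have to be settled first.

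Items 1 to 3 change wording and analysis only and need no new data. The cost is wider intervals, because level and trend must be separated, and a less favourable claim. Item 4 carries a real data cost, and the first three do not depend on it.

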## Discussion

Surgery is the main treatment modality for stages I–III colorectal cancer and frequently represents the most effective choice even in a palliative setting. Despite massive improvements in perioperative care and techniques, colorectal cancer surgery is still associated with a significant burden of postoperative complications which result in greater healthcare costs and severe functional sequalae for patients. If the value of healthcare is maximizing quality care at minimal cost [33], the large-scale participation in an audit, which constantly measure the care quality and the resources used associated for a benchmark feedback, represents a unique opportunity to significantly improve healthcare and limit expenditure.

Administrative data have already revealed their limitations when used to evaluate quality of care and can lead to misinterpretation when used to measure composite postoperative outcomes of complex and/or frail patients [34, 35]. However, together with mortality registries, they are essential for quality check control (enrollment rate) and completeness of data entry for specific items (re-admission rate, emergency department admission after discharge): for this reason, they were integrated into the entire ESCA auditing process.

Clinical data are more difficult and expensive to collect than administrative data, but these challenges are far outweighed by the opportunity clinical data can create in obtaining reliable information on the entire clinical process, ultimately improving quality and reducing hospital costs, as has been demonstrated by previously validated large national clinical audits such as NSQuIP [36] and DCRA [10]. The Dutch experience, thanks to the inclusion of the entire colorectal surgery population, represents to date, the most meaningful one given its “real-world” nature without selection bias and with risk-adjusted outcome data.

ESCA is an initiative which follows one of the main recommendations of the European Cancer Care Organization (ECCO) — Essential Requirements for Quality Cancer Care (ERQCC). The ERQCC recommended that clinical and process outcome data should be systematically measured and collected to give high quality care to patients [37].

With the paramount of a concrete enhancement of postoperative outcomes and a reduction of costs, ESCA aims to investigate, for the first time in Italy, the impact of systematic clinical auditing and feedback in the field of colorectal cancer surgery among a large population representative of a real-world population. Key performance indicators based on evidence-based guidelines, web-based registration of clinical data made by physicians integrated with administrative data and continuous feedback on the enrolment, and risk-adjusted outcomes are the critical elements of the study, which will provide strong and reliable data to measure and improve quality of colorectal cancer surgical care.

Future challenges will be to enhance this project at regional or national level and will use our experience to set regional and national quality standards.
